### **4.2.2 Handling of Withdrawals**

Patients are free to withdraw from the study at any time. Patient participation in the study may be stopped at any time at the discretion of the Investigator or at the request of the Sponsor.

Since this study includes the provision of gene therapy as a single administration, all patients who receive investigational product should be strongly encouraged to complete visits for a minimum of AEs assessments, even if these happen via phone visit.

If a patient who received investigational product withdraws prematurely from the study for any reason, study site personnel should make every effort to complete the full panel of assessments scheduled for the end of treatment visit. Patients who withdraw during the treatment period will complete the Month 12 (Year 1) assessments, while patients who withdraw during the follow-up period will complete the Month 60 assessments. If the termination visit is more than 3 months prior to the scheduled Month 12 assessment, or more than 6 months prior to the Month 60 assessment for subjects who discontinue participation after Month 12, in addition to performing termination visit assessments, the investigator and study site personnel should make every effort to complete the Month 12 or Month 60 assessments, respectively, at the originally scheduled time points. The reason for patient withdrawal must be documented in the eCRF.

If a patient undergoes the administration procedure but for whatever reason does not receive investigational product, the patient may be withdrawn from the study with safety follow-up for 30 days.

In the case of patients being lost to follow-up, at least 3 documented attempts to contact the patients must be made and documented in the patients' medical records.

### **4.2.3 Replacements**

Withdrawn patients will not be replaced.

### **4.2.4 Study Stopping Rules**

Each patient will receive only 1 dose of PR006A once during the course of the study; hence, stopping rules apply only during the Screening Period. Patients who have been dosed with PR006A will be followed to the end of the study as per protocol.

If any one of the following criteria are met, PR006A dosing will be paused and further enrollment across all study sites will be halted until the iDMC evaluates all available study data and makes a recommendation:

- More than  $5 \times$  ULN increase in ALT, AST, or both in any patient after PR006A administration that is not manageable by corticosteroid treatment implemented according to AASLD guidelines ([Manns et al 2010](#)).
- The occurrence of 2 or more of any 1 of the following treatment-emergent AEs (TEAEs)/SAEs (not 2 single occurrences of different AE/SAE):
  - Subarachnoid hemorrhage, cerebral macrohemorrhage
  - Grade 3 and/or 4 allergic reactions, hypersensitivity reactions, cytokine release reactions
  - Persistent neurological symptoms at least possibly attributable to the ICM investigational product administration procedure
  - CNS infections (e.g., meningitis, encephalitis)
  - Seizures, stroke, or acute paralysis
- More than 1 patient experiences any Grade 3 or higher AE that is judged as definitely, probably, or possibly attributed to PR006A.
- More than 1 Grade 3 or higher SAE that may or may not be potentially related to PR006A and that poses either an immediate risk to the patient's health or is likely to adversely affect the patient's long-term health.
- Death of a patient, after having received PR006A, that is judged as definitely, probably, or possibly attributed to PR006A. The study will be temporarily stopped in order to undergo review by the institutional review board (IRB)/independent ethics committee (IEC), iDMC, and other health authorities.
- The occurrence of a malignancy at any point after gene transfer that is judged per the Sponsor's final causality assessment as related to PR006A.

The study may be terminated if one or more of the following criteria are met:

1. The Sponsor decides to terminate the study based upon an assessment of safety.
2. The Sponsor decides to terminate the study for administrative reasons.

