### **Rationale for immunosuppressant regimen**

Intracisternal administration has been chosen to maximize the distribution of PR006A throughout the CNS and minimize systemic exposure to the viral capsid of AAV9 and the T-cell response, but inevitably there will be some escape of the virus out of the CSF and into the blood. In clinical studies, gene therapy candidates using AAV9 have been generally well-tolerated. Transient elevations in alanine aminotransferase (ALT) and/or aspartate aminotransferase (AST) levels, which respond to corticosteroid treatment, have been observed to occur approximately 3 weeks after treatment ([Mendell et al 2017](#)). Additionally, the second immunosuppressive agent, sirolimus, has been shown to suppress AAV-related and transgene protein expression-related immune responses in NHPs ([Mingozzi et al 2007](#); [Ramsingh et al 2018](#)), is reported to be beneficial in animal models of FTD ([Wang et al 2012](#)), and has a manageable safety profile which is considered steroid-sparing ([Pidala et al 2020](#)).

Therefore, in order to mitigate ALT and/or AST elevations, inflammatory changes in the CSF or other suspected immune system reactions, 1 loading dose of 6 mg oral sirolimus will be administered at Day -1, as well as a single dose of 1 g intravenous (IV) methylprednisone at Day 0. A concomitant maintenance dose of 2 mg/day sirolimus will be administered orally for 90 days starting at Day 0, which will then be tapered over the ensuing 15 to 30 days. The maintenance dose is administered to achieve trough levels of 4 ng/mL (range 2 to 8 ng/mL). One day after treatment with PR006A, patients will start prednisone 30 mg orally for 14 days followed by a 7-day taper.

At the Investigator's discretion, higher doses, a longer taper, or re-initiation of immunosuppressive treatment may be used (e.g., in cases of elevated AST or ALT, inflammatory changes in the CSF, or other suspected immune system reactions).

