## **5.5 Investigational Product Administration**

### **5.5.1 Immunosuppressant Administration**

#### **5.5.1.1 Corticosteroid Administration**

Subjects will receive a loading dose of methylprednisolone 1 g IV pulse on Day 0. Prednisone at a dose of 30 mg/day will be given orally as concomitant medication from Day 1 for 14 days, which will be then tapered over the ensuing 7 days. At the Investigator's discretion, higher doses or a longer taper of corticosteroids may be used.

Mitigation of risks associated with use of corticosteroids, including monitoring for AEs that may be related to corticosteroid use are described in [Section 6.2.2.2](#).

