#### **5.5.1.3 Immunosuppression Monitoring Criteria**

In addition to monitoring sirolimus trough levels, the Investigator should evaluate patient's clinical status, lab findings and potential AEs.

Consideration should also be given to the need to increase doses of the immunosuppressant agent, prolong the tapering regimen, add a third agent or re-initiate treatment based on clinical signs or symptoms consistent with an immune response, including:

- Asymptomatic pleocytosis with WBC > 30 mm^3 and/or high CSF protein (> 70 mg/dL)

- CSF pleocytosis and/or increased protein accompanied by clinical symptoms (including decompensation of underlying FTD symptoms)
- Emergence of sensory symptoms based on neurological examination and/or TNAS.
- ALT and/or AST elevation  $>5 \times$  ULN in conjunction with hepatitis symptoms (e.g., jaundice, fatigue)
- ALT and/or AST elevation  $>10 \times$  ULN irrespective of the presence or absence of clinical symptomatology

The Investigator should consider implementing a longer prednisone taper over an additional 4 weeks in patients presenting with ALT and/or AST  $>3 \times$  ULN at the end of the initial 14-day taper. In case of AST/ALT elevations refractory to prednisone treatment, the Investigator should seek expert advice from a hepatologist.

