#### **6.2.2.4 Risks Associated with AAV9-Based Therapy**

The viral capsid of AAV9 may trigger the innate and adaptive immune system. Overall, products (investigational and marketed) using the AAV9 vector have been safe and generally well tolerated in over 500 patients. Out of an estimated 21 clinical trials investigating AAV9-based gene therapies, 7 use an IT route of administration with approximately 60 patients having received an investigational therapy. The mode of administration via CSF is intended to minimize systemic exposure, but inevitably there will be some escape of virus out of the CSF into the blood. In clinical studies, gene therapy candidates using AAV9 have been generally well tolerated. Transient elevations in AST and/or ALT, which respond to corticosteroid treatment, have been reported ([Mendell et al 2017](#)).

Pleocytosis and increased protein in the CSF was observed in one patient dosed with PR001A (Prevail's AAV9-based gene therapy candidate delivering the GBA1 gene to subjects suffering from PD-GBA). Steroid-responsive CSF pleocytosis has been reported in another gene therapy trial utilizing AAV9 viral vector to deliver GAN gene to the patients suffering from giant axonal neuropathy (NCT02362438) ([Bharucha-Goebel et al, 2020](#)).

To mitigate the risk of potential capsid and other related immune reactions, the prophylactic course of immunosuppressive treatment (consisting of corticosteroids and sirolimus) should be followed as specified in the protocol. In cases of elevations of liver enzymes, inflammatory changes in the CSF or other suspected immune reactions to PR006A, higher doses, prolongation or re-initiation of immunosuppressive treatment may be considered at the discretion of the principal investigator. Risk mitigation for the immunosuppressive regimen is discussed in [Section 6.2.2.2](#).

While minimal axonal degeneration and gliosis limited to the dorsal funiculus as well as minimally increased cellularity in small clusters occurred in the DRG of few PR006A-treated NHPs, these findings were non-inflammatory, limited in their extent, and without clinical correlate, and therefore deemed non-adverse (PRV-2018-028). It is not predicted that the non-adverse findings in the NHPs will clinically translate to human patients. Notwithstanding, the protocol will exclude individuals with clinical evidence of peripheral symmetric sensory polyneuropathy and incidence of sensory symptoms will be monitored

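### One patient's ALT/AST above 5 x ULN pauses dosing only after corticosteroid failure, yet steroids beyond the prophylactic course are at the investigator's discretion, so a persistent rise given no further steroids need not meet the rule (minor)

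*Protocol*

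**What the plan says.** Protocol Section 4.2.4 halts dosing and enrolment at all sites until the iDMC has made a recommendation. Its first criterion is ALT, AST or both above 5 x ULN in any one dosed patient "that is not manageable by corticosteroid treatment implemented according to AASLD guidelines". Two other bullets could take in a liver event. One applies when "More than 1 patient experiences any Grade 3 or higher AE" attributed to PR006A. The other needs "More than 1 Grade 3 or higher SAE" that threatens the patient's health.

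The mandated oral steroid course is in Section 5.5.1.1: prednisone 30 mg/day from Day 1 for 14 days, "which will be then tapered over the ensuing 7 days". Beyond it:

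- Section 1.2.5 (immunosuppressant rationale) says that, at the investigator's discretion, "higher doses, a longer taper, or re-initiation of immunosuppressive treatment may be used".
- Section 6.2.2.4 says that "re-initiation of immunosuppressive treatment may be considered at the discretion of the principal investigator".
- Section 5.5.1.3 asks the investigator to consider stepping up treatment "based on clinical signs or symptoms consistent with an immune response, including" a list of findings. The liver items are a rise above 5 x ULN with hepatitis symptoms, or above 10 x ULN with or without symptoms. It also advises considering 4 more weeks of prednisone taper if ALT or AST exceeds 3 x ULN "at the end of the initial 14-day taper".

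**The concern.** The automatic single-patient trigger depends on a treatment having been tried and having failed, while the decision to give that treatment is left open. A raised value that the investigator only watches produces no evidence of steroid failure, so the criterion can stay unmet however long the value remains high.

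This matters because transaminase elevation is the one specific safety signal that Section 1.2.3 anticipates, at about 3 weeks. The product is a one-time gene therapy in a first-in-human trial. A rule that does not register the event would let further patients be dosed before the iDMC has been asked to look.

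The taper wording raises a smaller, separate question: on which day is the 3 x ULN check meant to be made?

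**Working it through.** The plan states no operating characteristic for this rule, so there is no figure to reproduce. The check compares the provisions and does some day counting.

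**1. The trigger.** Pause = (ALT or AST above 5 x ULN after dosing) AND (not manageable by corticosteroids given per the cited guideline). The second condition can be shown only if steroids have been given.

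**2. When the protocol itself requires steroids.**

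| Provision | Status |
|---|---|
| 5.5.1.1, prophylactic course | required |
| 1.2.5, higher dose, longer taper, restart | discretionary |
| 5.5.1.3, step-up list | for consideration, list not exhaustive |
| 5.5.1.3, longer taper above 3 x ULN | should be considered |
| 6.2.2.4, higher dose, prolongation, restart | discretionary |

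Nothing after the prophylactic course is mandatory in the protocol's own text.

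**3. The liver examples in 5.5.1.3 against the pause threshold.**

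| ALT/AST | Symptoms | Above the pause threshold? | Named in the 5.5.1.3 list? |
|---|---|---|---|
| 5 to 10 x ULN | no | yes | no |
| 5 to 10 x ULN | hepatitis symptoms | yes | yes |
| above 10 x ULN | either | yes | yes |

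The first row is where observation without further steroids is most plausible.

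**4. The other bullets.** The AE bullet needs at least 2 patients and the SAE bullet at least 2 SAEs. One patient with one isolated elevation meets neither. Section 6.5 makes ALT/AST above 3 x ULN an SAE only when bilirubin or INR is also raised, and that would still be a single SAE.

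**5. Who falls in the gap.** The plan is 3 cohorts of 5 (Section 7.4), 3 x 5 = 15 patients. Two per cohort are staggered, 3 x 2 = 6; three are not, 3 x 3 = 9. The stagger is 8 x 7 = 56 days and the expected onset about 3 x 7 = 21 days, which leaves 56 - 21 = 35 days before the next dosing in that cohort. An elevation at the expected time in either of the first two patients is therefore visible before the cohort proceeds. The exposure lies with the other three and with rises after Day 56. As one example of late timing, sirolimus ends at 90 + 15 = Day 105 to 90 + 30 = Day 120, beyond the stagger window.

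**6. Probability.** The protocol gives no rate for such elevations or for how often they would go without further steroids. A binomial calculation would rest on invented rates. It would also omit the existing pause for steroid-refractory cases, so none is offered.

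**7. The taper.** Full dose runs Days 1 to 14 and the taper Days 15 to 21 (14 + 7 = 21). The phrase in 5.5.1.3 joins 14 days to the word taper and can be taken as Day 14, the end of full dose, instead of Day 21: a difference of 21 - 14 = 7 days. Table 13-1 has chemistry at both visits, so the two readings point to different scheduled draws.

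**The case against.** **The guideline may close the gap.** Section 4.2.4 names a treatment standard, and not reproducing a cited guideline is no error. If it fixes when steroids start, the untreated case should not arise. This stands as a condition on the point. It would not remove the need to clarify, because 1.2.5 and 6.2.2.4 would then leave to discretion what 4.2.4 treats as settled.

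**The exemption looks deliberate.** The protocol describes transient rises that respond to steroids, and sparing those from a study-wide halt is sensible. That stands, and it is why the pause itself should not be widened.

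**Steroids would probably be given.** Sections 1.2.5 and 6.2.2.4 name raised liver enzymes as a reason for more immunosuppression, and 5.5.1.3 advises considering a longer taper above 3 x ULN near the expected onset. A rise before about Day 21 occurs under mandated steroids and could be read as steroid failure. All of this narrows the case.

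**Other safeguards exist.** Section 1.2.3 set the 8-week interval with this signal in mind. Transaminitis is among the primary safety endpoints that the iDMC assesses, and the iDMC may recommend changes or termination on the nature or severity of events. Clinically significant unexplained values are repeated and followed (6.5). A second patient's Grade 3 event of any kind attributed to PR006A triggers a pause, and 6.2.1.10 counts events starting within 1 month as at least possibly related. These stand. None requires prompt iDMC review of one isolated, persistent elevation not given further steroids.

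**Stronger readings to avoid.** A reader might infer that the protocol tells investigators not to treat a symptom-free rise of 5 to 10 x ULN. It does not: the list in 5.5.1.3 is open-ended and does not gate the pause rule. A reader might infer that such a rise would escape the iDMC altogether. The stagger and the endpoint reviews say otherwise. A reader might also take the taper phrase to mean Day 28 (14 + 14). The Synopsis, Sections 1.2.5, 3.1.1, 5.5.1.1 and 6.2.2.2, and footnote c of Table 13-1 all give a 7-day taper, so that reading is not credible.

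**Conclusion.** The point holds in a narrow form, as a minor one. On the protocol's own text, one patient's persistent ALT/AST elevation above 5 x ULN, not treated with additional corticosteroids, need not meet the pause rule, and no other provision requires prompt iDMC review of it. At full enrolment this mainly concerns 9 of 15 patients (the 3 unstaggered in each cohort), plus rises in any patient after the 8-week interval.

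This assumes that the cited guideline does not itself fix when to treat, which the documents do not show, and that bilirubin and INR are not raised. How often the case would occur cannot be stated.

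The taper phrase in 5.5.1.3 is wrong as written and rests on no assumption. It is an editorial slip in a sentence that times a clinical check, and chemistry is drawn at both candidate visits regardless.

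**What to change.** In Section 4.2.4, keep the automatic pause for steroid-refractory elevations and add: *A confirmed post-dose ALT or AST above 5 x ULN that persists on repeat testing and is not being treated with additional corticosteroids prompts expedited iDMC review.* Mirror it in the iDMC charter. This brings the uncovered case to the committee without an automatic halt, and leaves out rises already being treated with additional steroids. The thresholds for considering steroids need no change.

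In Section 5.5.1.3, change "at the end of the initial 14-day taper" to *at the end of the 7-day taper (Day 21 visit)*, so that the 3 x ULN check agrees with Section 5.5.1.1.

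The cost is one sentence, one phrase and an occasional ad hoc iDMC review, sometimes for a rise that would have settled unaided.

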#### **6.2.1.4 Reporting Adverse Events**

All AEs reported or observed during the study, as detailed in [Section 6.2.1.3](#), will be recorded on the AE page in the eCRF. Information to be collected may include but is not limited to the following:

- drug treatment
- dose
- event term
- time of onset
- Investigator-specified assessment of severity and relationship to investigational product
- time of resolution of the event
- seriousness
- any required treatment or evaluations
- outcome

Adverse events resulting from concurrent illnesses, reactions to concurrent illnesses, reactions to concurrent medications, or progression of disease states must also be reported. All AEs will be followed to adequate resolution. The Medical Dictionary for Regulatory Activities (MedDRA) will be used to code all AEs.

Any medical condition that is present at the time that the patient is screened but does not deteriorate should not be reported as an AE. However, if it deteriorates at any time during the study, it should be recorded as an AE.

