### **6.2.1.5 Suspected Adverse Reactions/Adverse Reactions**

The following AEs will be considered as ARs:

- All AEs occurring within 1-month post-PR006A administration procedure
- All AEs assessed as at least possibly related to the injection procedure or to investigational product treatment by the Investigator or Sponsor
- All AEs for which the Investigator's causality assessment is missing or indeterminate

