#### **6.2.1.10 Assessment of Causality**

The Investigator's assessment of an AE's relationship to investigational product is part of the documentation process, but it is not a factor in determining what is or is not reported in the study. If there is any doubt as to whether a clinical observation is an AE, the event should be reported.

The relationship or association of the investigational product or the ICM administration of the investigational product in causing or contributing to the AE will be characterized using the following classification and criteria:

- **No** (unrelated, not related, unlikely to be related) – The time course between the administration of investigational product and the occurrence or worsening of the AE rules out a causal relationship and another cause (concomitant drugs, therapies, complications, etc.) is suspected.
- **Yes** (possibly, probably, or definitely related) – The time course between the administration of the investigational product and the occurrence or worsening of the AE is consistent with a causal relationship should be considered at least possibly related to investigational product or investigational product administration procedure. This is defined as all AEs that begin during or within 1 month following investigational product administration, plus all AEs regarded by the Investigator or Sponsor as at least possibly related to investigational product or investigational product administration procedure, plus all AEs for which the Investigator's causality assessment is missing or indeterminate.

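### The single-death pause in 4.2.4 covers only deaths attributed to PR006A, so one late death attributed to the required immunosuppression forces no automatic pause; for procedure deaths the wording is unclear

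*Protocol*

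**What the plan says.** Protocol 4.2.4 lists events that pause PR006A dosing and halt enrolment at all sites until the iDMC has reviewed the data and made a recommendation. The death bullet needs one event and is limited by cause: "Death of a patient, after having received PR006A, that is judged as definitely, probably, or possibly attributed to PR006A". The broadest other bullet has no cause limit but needs two events: "More than 1 Grade 3 or higher SAE that may or may not be potentially related to PR006A", with the further condition that the event threatens the patient's immediate or long-term health.

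The same list names the injection procedure as a cause of its own in the neurological item: "Persistent neurological symptoms at least possibly attributable to the ICM investigational product administration procedure".

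The causality sections treat product and procedure together. Section 6.2.1.5 counts as adverse reactions "All AEs assessed as at least possibly related to the injection procedure or to investigational product treatment by the Investigator or Sponsor". Section 6.2.1.10 says that what is classified is "The relationship or association of the investigational product or the ICM administration of the investigational product in causing or contributing to the AE", on a scale with only two classes, *Yes* and *No*. The *Yes* class takes in every event that starts within 1 month of administration and every event whose causality is missing or indeterminate. Neither section has a category for the immunosuppressants.

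Section 6.2.2.2 requires sirolimus for 90 days plus a 15 to 30 day taper, together with a short corticosteroid course, and acknowledges that the regimen can have fatal effects.

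**The concern.** Patients in this first-in-human study receive the ICM injection and the immunosuppression only because they take part. A death from either is a death from the study intervention, and one such death would normally be reason enough to stop and look before dosing the next patient. The death bullet does not require that if the cause is judged to be the immunosuppression and not PR006A. Whether it requires it for the procedure depends on which section one reads.

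What is at stake is the automatic step. Without it, the decision to hold dosing after such a death is left to discretion, and whether the rule applies has to be argued after the event.

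**Working it through.** No figure in the plan needs reproducing. The check has four parts.

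**1. Each bullet of 4.2.4 against one death attributed to immunosuppression and judged unrelated to PR006A.**

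| Bullet | Events needed | Cause limit | Result |
|---|---|---|---|
| ALT/AST above 5 × ULN, not controlled by corticosteroids | 1 | none | met only if the death involved such an elevation |
| Listed events (hemorrhage, CNS infection, stroke and others) | 2 of the same kind | none, except the neurological item | at most 1 of 2 |
| Grade 3+ AE | more than 1 patient | PR006A | not counted |
| Grade 3+ SAE with risk to health | more than 1 | none | 1 of 2 |
| Death | 1 | PR006A | not met |
| Malignancy | 1 | PR006A | not met |

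Taken alone, such a death forces no pause outside the liver case. It does so if another qualifying Grade 3+ SAE has occurred, in any patient and of any cause, or a second listed event of the same kind.

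**2. When such a death could be judged unrelated to PR006A.** Inputs are the regimen (5.5.1.1, 5.5.1.2, 6.2.2.2) and the 1-month default (6.2.1.10).

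- Corticosteroids: methylprednisolone on Day 0, prednisone on Days 1 to 14, taper on Days 15 to 21. The planned course is over by Day 22, inside the default window.
- Sirolimus: 90 + 15 = Day 105 to 90 + 30 = Day 120. Taking a month as 30 days, 105 − 30 = 75 to 120 − 30 = 90 days of exposure fall after the default has lapsed.

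The realistic case is therefore sirolimus, or corticosteroids extended by the Investigator, with onset after Month 1. The definition of *No* is strict: the time course must exclude the product and another cause must be suspected. Concomitant drugs are among its examples of another cause. Its label is looser, since it reads "unrelated, not related, unlikely to be related".

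**3. Procedure deaths, sections side by side.**

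- 4.2.4 names the procedure in the neurological item and omits it from the death bullet. Read within that section, PR006A means the product only.
- 6.2.1.10 has one *Yes* class for product or procedure. Its label uses the same three grades (possibly, probably, definitely) as the death bullet. Read this way, a procedure death is already covered.
- 6.2.1.4 mentions "Investigator-specified assessment of severity and relationship to investigational product" and not the procedure, but presents its list as non-exhaustive, so it settles nothing.

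**4. How many patients could be dosed before the next iDMC review.** Inputs are 3 cohorts of 5 (7.4), 8-week gaps, and escalation in parallel with patients 3 to 5 (3.1.1, 11.1.1), with each later cohort following the Cohort 1 design. The fastest schedule, in days from the first dosing, is:

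- Cohort 1: 0, 56, 112 (three patients)
- Cohort 2: 112, 168, 224 (three patients)
- Cohort 3: 224, 280, 336 (three patients)

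With reviews only 8 weeks after each cohort's second patient (Days 112, 224, 336), dosings per interval are 2, 3 + 2 = 5, 3 + 2 = 5, and 3, which total 15. Slower enrolment spreads these dosings out but does not change the counts, so a death just after a review could be followed by up to 5. On the fastest schedule, a death on Days 113 to 167 is followed by 1 (Day 168) and a death on Days 168 to 223 by 0.

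If the iDMC also reviews in each cohort's first 8-week gap (Days 56, 168, 280), the intervals are 1, 1, 4, 1, 4, 1, 3, again 15. The maximum is then 4. On the fastest schedule those 4 are dosed on one day, which leaves 0.

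**The case against.** The strongest reply is that the gap hardly exists. Most procedure complications would start within a month and so fall into the pooled *Yes* class. *No* is hard to justify for a one-time vector that expresses its transgene constitutively. A death also counts towards the any-cause SAE bullet, SAEs must be reported within 24 hours (6.2.1.7), the iDMC may recommend changes or termination (11.1.1), the Sponsor may stop at any time (11.3), and the iDMC charter, which is not at hand, may add ad hoc meetings. Most of this stands, and it limits the point to a clarification. It does not close the immunosuppression case, because the scale has no place for that regimen and these powers are discretionary.

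A reader might infer that procedure deaths definitely escape the rule. The documents do not support that, because 6.2.1.10 can bring them in. Nor does 6.2.1.4 show that attribution to the procedure goes unrecorded.

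A reader might also infer that the neurological item has the same defect, since it names only the procedure and so leaves out mild symptoms attributed to the vector. That is a choice of threshold, not an error. Section 4.2.4 handles events attributed to PR006A by severity (Grade 3 or higher in more than one patient), and "Seizures, stroke, or acute paralysis" count whatever their cause. Lower-grade sensory symptoms are followed with the TNAS and have management steps in 5.5.1.3 and 6.2.2.4. The related primate findings were deemed non-adverse (1.3). Whether to pause a study for two mild sensory complaints is open to debate.

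A last objection is that naming the procedure in the death bullet sharpens the contrast with the Grade 3+ AE bullet, which names only PR006A. That is fair but small, since the neurological item already draws the distinction.

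**Conclusion.** The point holds in a narrow form. One death attributed to the protocol-required immunosuppression and judged unrelated to PR006A forces no automatic pause unless another qualifying Grade 3+ SAE has occurred or another bullet happens to apply. For ICM-procedure deaths the rule is ambiguous and not shown to be absent.

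The size is 0 to 4 further dosings before the next review, or at most 5, depending on when the death falls and on whether the iDMC reviews in each cohort's first 8-week gap. Section 3.1.1 says the staggering exists to permit iDMC review, so the lower range is the better supported. These counts assume all three cohorts enrol 5 patients in the planned sequence and that nobody uses discretionary powers in the meantime. The protocol gives no rate for such deaths, so no probability can be attached.

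Severity: minor safety clarification.

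**What to change.** In the death bullet of 4.2.4, keep the three grades of attribution and extend the cause to PR006A, the ICM administration procedure, or the protocol-required immunosuppression. For deaths, record attribution to each of the three separately. Leave the neurological item and all other bullets and thresholds as they are.

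The cost is one reworded bullet, matching text in the iDMC charter, and one attribution entry for deaths. The downside is a possible extra temporary pause for iDMC review after a death.
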